### Study setting

From 2001 to 2014, Odisha and Maharashtra bore the burden of about 40300 and 56000 snakebite deaths with an age-standardized death rate of 6.7 and 3.5 / 100000 respectively [8]. Deaths between the age of 5 to 14 years were greater in Odisha while deaths among females were prominent in Maharashtra [8]. SBE has been a chronic problem in these two states with an earlier county-wide survey (1941–1945) suggesting that compared to other states, snakebite mortality is a greater problem here as the majority of geographical areas are forested and infested with snakes [29]. The proposed study is a multi-center study that will be conducted in the West and East Zones of India. Under the West zone (Maharashtra state), two blocks namely, Shahapur in district Thane and Aheri in district Gadchiroli will be included. Under the East zone (Odisha state), two blocks namely, Khordha in district Khordha and Kasipur in district Rayagada will be included (Fig 3, Table 1). The population in the study areas lives with an absolute risk of ≥0.5% of dying due to snakebite before the age of 70 years with the risk being highest in Aheri and Kasipur [8].

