**Fig 3 pone.0281809.g003:**
[figure not shown]
Geographical location of study areas of Maharashtra and Odisha states in India. Source: AMCHARTS SVG Maps; https://www.amcharts.com/svg-maps/?map=india2019. Permission obtained for use.

**Table 1 pone.0281809.t001:** Demographic details of the study areas in Maharashtra and Odisha.

Parameter	Shahapur block	Aheri block	Khordha block	Kasipur block
Coordinates	19.45°N 73.33°E	19.41°N 80.00°E	20.16°N 85.66°E	19.22°N 83.08°E
Population	314103	116992	139978	70542
Living in rural areas	77.5%	87.5%	67%	100%
Scheduled Tribes population	35.7%	49.8%	8.4%	58.8%
Female literacy	58.41%	55.67%	73.22%	20.35%
Sex ratio	957	986	935	1071
Workers engaged in marginal activities*	27.6%	29.8%	25.5%	60%

All data sourced from—Census of India 2011. Registrar General and Census Commissioner of India. https://www.censusindia.co.in/. Accessed 24 April 2022.

*Marginal activities provide livelihood for less than six months in a year. Proportions out of total working population in the block

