### Statistical analysis

The baseline data will be analyzed separately for different strata (Gender-wise, Age-wise, seasonal variation, distribution of venomous and non-venomous snakebite, site of snakebites, and categorization of snakebite based on the sign and symptoms of envenomation). The differences across strata will be investigated using appropriate statistical tests based on the nature of the variables. The Chi square and Fisher’s Test would be used to compare categorical variables while the independent t-test would be used to compare continuous variables. To check the factors associated with the incidence of snakebite, bivariate regression models will be used and results will be presented through odds ratios. The primary outcome will be reduction in the incidence of snakebite cases per 100000 population and a reduction in the case fatality rate in the study areas at the end of two years, measured by comparing the pre- and post-intervention data on the incidence of snakebite and mortality in the four study blocks. The secondary outcomes will include reduction in mean bite to needle time, reduction in the proportion of snakebite victims referred to higher facilities for management, increase in the proportion of MOs providing treatment as per STG 2017, mean increase in the number of vials of anti-venom administered to victims, reduction in the proportion of cases with severe complications including reduced kidney failure and amputation rate. Data from interviews of healthcare providers will be analyzed further for frequency. A summative index will be developed from the knowledge test of health workers. Two sample t-test will be used to compare the change in the knowledge of Medical Officers and the healthcare workers after the training. A p-value < 0.05 will be considered statistically significant. All the quantitative data will be entered and analyzed using the statistical package SPSS (version 26.0; IBM Corporation, Armonk, NY, USA).

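### The only regression named for factors associated with snakebite incidence takes one factor at a time, so odds ratios pooled over four very different blocks may be confounded by block

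*Protocol article*

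**What the plan says.** The Statistical analysis section introduces this analysis with the words "To check the factors associated with the incidence of snakebite" and then fixes the method: "bivariate regression models will be used and results will be presented through odds ratios". I read bivariate as one factor and one outcome per model. No other regression is named for this question. The section's general threshold is "A p-value < 0.05 will be considered statistically significant".

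The same section plans stratified description of the baseline data, beginning "The baseline data will be analyzed separately for different strata (Gender-wise, Age-wise, seasonal variation". The list goes on to type of bite, site of bite, and signs and symptoms. Block is not in it.

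Study setting reports the absolute risk of dying from snakebite before age 70 in the study areas, "with the risk being highest in Aheri and Kasipur". It also gives the two states, Odisha and Maharashtra, an "age-standardized death rate of 6.7 and 3.5 / 100000 respectively". Table 1 gives census figures by block, including the row "Scheduled Tribes population".

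**The concern.** A variable confounds a crude association when it is linked both to the outcome and to the factor under study. Block is a natural candidate here. Table 1 shows that block is strongly linked to population make-up: tribal share, female literacy (20.35% to 73.22%) and marginal work (25.5% to 60%) all differ widely. The two blocks that the article names as having the highest risk of snakebite death also have the two largest tribal shares and the two largest shares of marginal work.

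If bite incidence also differs by block and the blocks are pooled, a factor with no effect inside any block can show a crude odds ratio away from 1. With enough cases it would pass the 5% threshold. An association reported as a feature of a group would then be, in part, a feature of where that group lives.

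**Working it through.** The article states no odds ratio, sample size or power for this analysis, so there is no figure to reproduce. The check asks how far a crude ratio moves when the true within-block effect is nil.

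**Inputs from Table 1**

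| | Shahapur | Aheri | Khordha | Kasipur | Total |
|---|---|---|---|---|---|
| Population | 314,103 | 116,992 | 139,978 | 70,542 | 641,615 |
| Tribal share | 35.7% | 49.8% | 8.4% | 58.8% | 34.9% |
| Tribal (population × share) | 112,135 | 58,262 | 11,758 | 41,479 | 223,634 |
| Non-tribal (remainder) | 201,968 | 58,730 | 128,220 | 29,063 | 417,981 |

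**Assumption.** Bite incidence by block is not given. I set it to 1 (relative) in Shahapur and Khordha and to m in Aheri and Kasipur, the same for tribal and non-tribal residents of a block.

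**Formula.** Let p₁ and p₀ be the fractions of tribal and non-tribal people who live in Aheri or Kasipur.

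- p₁ = (58,262 + 41,479) / 223,634 = 0.446
- p₀ = (58,730 + 29,063) / 417,981 = 0.210
- Crude ratio = [1 + (m − 1)p₁] / [1 + (m − 1)p₀]

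**Results**

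- m = 1: 1.00
- m = 1.5: 1.223 / 1.105 = 1.11
- m = 2: 1.446 / 1.210 = 1.20
- m = 3: 1.892 / 1.420 = 1.33

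Bites are rare at the incidences tried, so the crude odds ratio agrees with this ratio to two decimals. The Mantel-Haenszel odds ratio stratified by block is 1.00 in every case, the value put in. The same calculation for marginal work gives 1.06, 1.11 and 1.18 at m = 1.5, 2 and 3. It applies the Table 1 shares, which are shares of workers, to the whole population as an approximation.

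**Would it reach p < 0.05?** Take a further assumed base incidence of 1 per 1000 and z = ln(OR) / √(1/a + 1/b + 1/c + 1/d), with a, b, c and d the cells of the expected pooled table. At m = 2 there are about 323 tribal and 506 non-tribal cases, the standard error is 0.071 and z is 2.5.

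| m | Expected cases | z, tribe | z, marginal work |
|---|---|---|---|
| 1.5 | 735 | 1.3 | 0.75 |
| 2 | 829 | 2.5 | 1.4 |
| 3 | 1,017 | 4.5 | 2.6 |

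Against a two-sided critical value of 1.96 (the article does not state sidedness), the null factor is expected to cross the threshold in some of these cases and not in others.

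**A different risk pattern.** Suppose incidence follows the state death rates instead, so that Khordha and Kasipur carry 6.7 / 3.5 = 1.91 times the risk of the two Maharashtra blocks.

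- Tribal fraction in the Odisha blocks = (11,758 + 41,479) / 223,634 = 0.238
- Non-tribal fraction = (128,220 + 29,063) / 417,981 = 0.376
- Crude ratio = (1 + 0.914 × 0.238) / (1 + 0.914 × 0.376) = 1.218 / 1.344 = 0.91

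The direction reverses for tribe. For marginal work the odds ratio is 1.07. Neither is significant at a base of 1 or 2 per 1000 (z for tribe is −1.3 and −1.9).

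**The case against.** The strongest defence is that this is one descriptive sentence. Identifying risk factors is not among the four objectives or the primary and secondary outcomes. The article is condensed, and an adjusted step may stand in the full protocol or analysis plan. The article does not say that the blocks are pooled in this model, and it separately plans descriptions by gender, age and season. All of this stands and limits the weight of the point. It does not remove it, because the article goes beyond silence: it selects the model type and the reported measure, and an analysis that followed the sentence would be unadjusted.

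Three stronger readings are tempting, and the article supports none of them.

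- A reader might infer that the article's own figures demonstrate strong confounding of bite incidence. They do not. Study setting speaks of the risk of dying from snakebite, which also depends on case fatality and access to care.
- A reader might infer that tribe or occupation will be reported as false risk factors. Neither is named as a model factor. They serve here as examples because Table 1 gives their shares, and the marginal-work contrast rests mainly on Kasipur (60%; Aheri is 29.8% against 27.6% and 25.5%).
- A reader might infer that community education would be aimed at the wrong groups. Phase II builds the educational material on what the focus groups reveal and on published literature, not on this model.

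A practical objection also stands. The data forms cover bitten patients only, so adjustment needs more than fields already on the form. But the bivariate model needs a comparison group or population denominator too; adjustment asks that the same source be split further.

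**Conclusion.** The point holds as a conditional one. The article names only one-factor models for factors associated with incidence and no adjustment for block, in a study whose blocks differ greatly in make-up and in risk of snakebite death. If the blocks are pooled and bite incidence is unequal, crude odds ratios may be confounded by block. With no true effect, the tribal ratio runs from about 0.91 (risk following the state death rates) to 1.33 (threefold incidence in Aheri and Kasipur).

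The size is modest. Its sign and significance depend on block incidences that the article does not give. The calculation rests on Table 1 census shares, on assumed incidence multiples and base rates, and on equal risk for tribal and non-tribal people within a block. The primary pre/post comparison of incidence and case fatality is not touched. Since the direction cannot be known in advance, the crude estimates cannot be corrected by judgement afterwards, which is reason enough to adjust.

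**What to change.** In the Statistical analysis section, replace the sentence on bivariate regression so that the main association estimates are adjusted for block, or stratified by block and combined. Add age group and sex where the comparison group or population denominator can be split by them. Report adjusted estimates with 95% confidence intervals, and show the bivariate estimates beside them, labelled descriptive.

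Do not enter season as a covariate unless person-time by season is defined, because an unbitten person has no season of bite.

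The cost is slightly wider intervals and the work of splitting denominators by block, age group and sex. Block itself is known by design.

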SBE burden coupled with a lack of awareness amongst the Medical Officers (MOs) and other healthcare providers about the National Snakebite Management Protocol (2009) and Standard Treatment Guidelines (STG, 2017) creates major hurdles in management of SBE [13]. An irrational usage of anti-venom skin test was also reported in the tribal block of Dahanu, Maharashtra [17]. Primary Health Centers in rural India face a multitude of problems including the acute shortage of trained human resources, unavailability of anti-venom and emergency ventilation services [18]. Issues with public health facilities and geographical inaccessibility supplemented by superstitions and cultural beliefs regarding snakes force SBE victims to seek care from faith healers [19, 20]. Studies in rural and tribal areas have revealed inadequate knowledge about venomous snake identification and faith healers were the first choice for about 38–68% of people for SBE management [17, 21–24]. Most of the traditional and herbal methods of first aid and management of snakebite have been found to cause more harm than benefit [25, 26]. Proper knowledge of snakes and snake-bite management was also found to be either diminutive or absent in the majority of participants as reported by a study from Haryana [27]. Fear, negativity, and unfamiliarity regarding prevention and ambivalent opinions on health-seeking are known drivers of people’s perception of snakes and snakebites [28]. These findings strongly suggest the need for community awareness on the prevention and first aid of snakebite and empowerment of frontline healthcare workers and Medical Officers for effective management of SBE in public healthcare settings.

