## Materials and methods

### Study scheme

The interventional study has retrospective, prospective, cross-sectional, and qualitative components and will be conducted in a community as well as hospital settings (Fig 1). It is divided into five phases (Fig 2). Phase I involves collecting retrospective data of snakebites, facility surveys, and focus group discussions (FGDs) in the community. Phase II is to increase awareness and empower the community on prevention, first aid, and early transport of snakebite patients to the nearest health facility. Phase III will be to evaluate the basic knowledge on snakebite management and anti-venom utilization among healthcare providers. Phase IV is to empower the health system for management of SBE and optimal utilization of anti-venoms through training programs and Phase V will focus on the impact evaluation of the health system and community interventions using FGDs and comparison of pre-and post-intervention data.

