#### Phase I–Retrospective data collection, facility surveys, and FGDs in the community

Two-year retrospective data (01 January 2020 to 31 December 2021) will be collected from all the public health facilities in study areas where snakebite management is expected to be provided. This includes all the Primary Health Centers, Rural Hospitals / Community Health Centers, Sub District Hospitals and District Hospitals. Medical Colleges where severe cases are referred from the study blocks will also be included to ensure quality retrospective data collection. Additional data on snakebite deaths will also be collected from local authorities, panchayat office, registrar of births and deaths so that maximum deaths are captured. A cross-sectional survey will assess the preparedness of the public health facilities for SBE management. Retrospective data and facility data will be collected and entered into an online application. The captured data will be verified at regular intervals by the study coordinator.

The qualitative component will involve conducting community FGDs in the study areas. Total 24 FGDs will be conducted, six per block (three male, three female). Each FGD will be restricted to 8 to 16 participants. Actual number of FGDs may vary according to the saturation of responses. FGDs will be conducted at common and acceptable community places. The Primary Health Centers (PHCs) in the block would be enlisted and one random village would be picked per PHC. The information about conduct of a FGD would be given to the villagers with the help of the frontline community healthcare workers and community leaders and 8–16 randomly selected participants would be invited to participate. Participants belonging to the community and above 18 years of age will be included for FGDs. Healthcare providers will be excluded.

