#### Phase II—Development and implementation of an educational intervention

Educational interventions in the form of printed IEC material will be developed based on the gaps identified during the FGDs and a review of the literature. The TAC will review the IEC material based on the relevance and ease of understanding for the target population. Commonly occurring words in the local language along with pictorial/cartoon messages will be used in the IEC material. Contact numbers of public health facilities will be included. Short information videos about immediate first aid and early referral will be developed and circulated among the community members. Videos regarding immediate care of a snakebite victim at the facility will be circulated among the healthcare providers. Pilot intervention procedures will be implemented to know the community’s understanding and accordingly further intervention procedures will be carried out by trained staff. The final revised version of the IEC will be assessed for ease of readability using the SMOG index. All educational tools will be validated with the help of the Technical Advisory Committee, herpetologists and subject experts.

IEC materials will be distributed at key places like village panchayats, forest departments, local faith healers, school teachers, community leaders, anganwadis, tribal residential schools, Sub-Centers (SCs), PHCs, and other health facilities. With the help of local health officials and ASHAs, community meetings and talks would be held at each study site during *gram sabha* (village gatherings), community program and religious events. Informative posters would also be put up at places where people gather routinely like tea stalls or local restaurants. Prevention measures to be employed for snakebite prevention in the communities will be as per the Standard Treatment Guidelines, (STG,2017).

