#### Phase V—Impact evaluation of interventions

FGDs will be conducted in the study areas to evaluate the post-intervention community knowledge with the same methodology as discussed in Phase I, two months after the educational intervention. Pre- and post-training evaluations will be done to assess knowledge retention and the impact of training on the healthcare providers. Prospective data will be collected from the health facilities after the capacity building training of Medical Officers in study blocks for a period of one year. Incidence and case fatality rate in the study blocks will be calculated based on the prospective data. The impact of capacity building on the healthcare system will be assessed by comparing prospective data with the retrospective (pre-intervention) data.

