From the community point of view, preventing life-threatening snakebite incidences is the holy grail. Simple measures including use of bed-net while sleeping, use of torch and stick while walking in the dark, ban on open defecation practices, using knee length footwear in farms can aid in prevention [43, 44]. Community engagement using an integrated approach that involves strengthening the knowledge and awareness supplemented by efforts to tackle the sociocultural and economic barriers to seeking early healthcare can improve the management experience of many victims [6, 33]. Establishment of useful referral mechanisms between various stakeholders including community members, key influential persons in the area, administrative bodies and the healthcare system can go a long way in dealing with the SBE burden.

The National Snakebite Project will use a multi-sectoral, multi-stakeholder approach to reduce the burden of SBE. Encouraging community participation, healthcare provider empowerment, and wide-scale IEC activities are the strengths of the study. Health facility based retrospective and prospective data collection might result in underreporting of the SBE burden. However, an effort would be made to collect data from municipal corporation records, gram panchayat, crematorium or any other institutions in the study areas to ensure that maximum snakebite deaths are captured in addition to hospital records. Further, the evidence generated from the study may be useful to the Government of India for developing national strategies to reduce SBE burden. Model clinical snakebite management centers can be established all over the country based on the outcome of this study. The engagement of community members, local authorities, healthcare providers, herpetologists, social scientists, and public health experts is envisioned to accentuate the efforts for the prevention and control of snakebites in India.

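### The incidence primary counts a fall in facility-recorded snakebites as success while the programme encourages facility attendance, so a true fall in bites can be masked

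*Protocol article*

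**What the plan says.** The Statistical analysis section sets the primary outcome and its direction: "The primary outcome will be reduction in the incidence of snakebite cases per 100000 population and a reduction in the case fatality rate". It is to be "measured by comparing the pre- and post-intervention data on the incidence of snakebite and mortality in the four study blocks". No comparison block is described.

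Both counts rest on facility records. Under Phase I, two years of baseline data (2020 and 2021) "will be collected from all the public health facilities in study areas where snakebite management is expected to be provided", with referral medical colleges added. Under Phase V, one year of data is taken from the health facilities after the training of Medical Officers, and "Incidence and case fatality rate in the study blocks will be calculated based on the prospective data". The section on data collection tools says that the retrospective and prospective forms are filled from hospital records.

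The programme also acts on attendance. The Study scheme gives Phase II the aims of prevention, first aid and "early transport of snakebite patients to the nearest health facility". Under Phase II, of the printed material: "Contact numbers of public health facilities will be included". That material also goes to local faith healers, and videos for the community cover early referral. The Introduction reports from rural and tribal studies that "faith healers were the first choice for about 38–68% of people for SBE management".

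The Discussion acknowledges that "Health facility based retrospective and prospective data collection might result in underreporting of the SBE burden". The remedy there (municipal, panchayat, crematorium and similar records), like the additional sources in Phase I, is directed at deaths.

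**The concern.** Under-reporting that stays the same cancels in a before-after ratio. Under-reporting that the programme itself reduces does not. Here the community component encourages bitten people to go where cases are counted, and success on the first primary outcome is defined as counting fewer of them. Prevention pushes the recorded rate down and better care-seeking pushes it up, and the planned data cannot separate the two. Nothing described corrects the count of non-fatal bites. These are nearly all of the incidence numerator: the Introduction cites a case fatality rate of 4.5% in tribal Maharashtra.

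At stake is a missed benefit. A programme that prevents bites and also improves attendance could report no change or a rise on a primary outcome meant to inform extension to other states.

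**Working it through.** The article gives no baseline incidence, target effect or power for this outcome, so there is no figure to reproduce. The check shows how far a change in capture can move the recorded rate.

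**Identity.** Recorded incidence = true incidence × c, where c is the share of bites that is recorded. So recorded ratio (post/pre) = true ratio × c1/c0. The true fall needed before any recorded fall appears is 1 − c0/c1.

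**Capture model (assumption).** Let f be the share choosing a faith healer first and r the share of those people who are recorded at a facility anyway. Everyone else is taken as recorded. Then c = 1 − f(1 − r).

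**Inputs.** The baseline values of f (38%, 50%, 68%) lie within the Introduction's 38–68%. The post-intervention values (28%, 25%, 34%) and r (0, 50%, 80%) are assumptions. The article gives none of these for the four blocks.

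| r | f: 38% to 28% | f: 50% to 25% | f: 68% to 34% |
|---|---|---|---|
| 0 | 0.72/0.62 = 1.16 | 0.75/0.50 = 1.50 | 0.66/0.32 = 2.06 |
| 50% | 0.86/0.81 = 1.06 | 0.875/0.75 = 1.17 | 0.83/0.66 = 1.26 |
| 80% | 0.944/0.924 = 1.02 | 0.95/0.90 = 1.06 | 0.932/0.864 = 1.08 |

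Entries are c1/c0. The true fall that each would fully hide:

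- r = 0: 14%, 33%, 52%
- r = 50%: 6%, 14%, 20%
- r = 80%: 2%, 5%, 7%

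**Example.** With a true 20% fall in bites and f going from 50% to 25%, the recorded ratio is 0.80 × 1.50 = 1.20 if r = 0 (an apparent rise). It is 0.80 × 1.17 = 0.93 if r = 50%, and 0.80 × 1.06 = 0.84 if r = 80%.

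**Direction.** If c1/c0 is above 1, the true ratio is smaller than the recorded ratio. A recorded fall then understates the true fall.

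**Case fatality rate.** The same shift acts on its denominator in the opposite direction. If every death were counted in both periods and the number of deaths did not change, the rate would drop by 1 − c0/c1, which is 2% to 52% across the table, with no life saved.

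**Expected deaths.** Using the Table 1 populations and the state rates under Study setting:

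- Maharashtra blocks: 314,103 + 116,992 = 431,095; × 3.5 per 100,000 = 15.1
- Odisha blocks: 139,978 + 70,542 = 210,520; × 6.7 per 100,000 = 14.1
- Total: 29.2 a year

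With two baseline years against one follow-up year (58.4 deaths against 29.2 if nothing changes), an exact two-sided 5% comparison of Poisson rates has power of about 12% for a 20% fall, 25% for 30% and 68% for 50%. This assumes complete death capture.

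**The case against.** The strongest reply is that the bias works against the programme. If attendance rises, a recorded fall in incidence is conservative evidence of a true fall. That stands as far as capture is concerned. A reader might infer that neither a rise nor a fall carries any information, but that does not follow from a model in which capture goes up. The ambiguity lies with a rise or no change.

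A second reply is that the sizes are hypothetical. This also stands. Choosing a healer first does not mean never reaching a facility, the article does not say how many go on to one, and every post-intervention share above is assumed. With most healer-first users recorded anyway, the distortion is only a few per cent.

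A third reply is that the Discussion already concedes under-reporting. This does not answer the point, because the concession does not reach a change between periods and the remedy covers deaths. Nor should the text be over-read: a reader might infer that the plan treats under-reporting as constant, or that it states an aim of drawing people away from healers. It is silent on the first. Its stated aims are prevention, first aid and early transport, and the shift away from healers is an inference from these.

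Finally, it is tempting to replace the case fatality rate with population mortality. The documents do not support that as a clear gain. Precision is poor. The Introduction reports that most deaths occur at home and that government data captured about 10% of expected deaths, so death capture may change too.

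**Conclusion.** The concern holds in this form: as fixed, the first primary outcome can report a programme that prevents bites as showing no change or a rise, because the cases counted depend on attendance that the programme promotes. The mechanism follows from the text. The size does not: under the assumed shifts the inflation runs from x1.02 to x2.06, depending mainly on how many healer-first users reach a facility anyway.

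A recorded rise or no change is uninterpretable as an effect on true incidence. A recorded fall would, if capture rose, be a lower bound on the true fall, leaving aside other reasons for change in an uncontrolled before-after comparison. A reader might go further and conclude that the programme will look like a failure. The documents do not support that, since prevention acts the other way and the net direction is unknown.

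**What to change.** In the Statistical analysis section and under Phase V:

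1. Rename the outcome as facility-recorded snakebites per 100,000 population. Analyse it two-sided with no direction of benefit.
2. State in advance that a rise or no change will not be read as failure of prevention, and that the change in this rate does not estimate the change in true incidence.
3. Add snakebite deaths per 100,000 block residents per year, using the same death sources in both periods (facilities, panchayat, registrar of births and deaths, and the other records named in the Discussion). Phase V names only facilities, so it must say this. Report the new rate beside the case fatality rate, not in its place, because it does not depend on the case denominator.

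The cost is an amendment to the outcome wording and to the registration, and the work of applying the death sources equally in both periods. The added mortality rate will be imprecise, at about 29 expected deaths a year, and its capture may also change. It should be reported with its interval and that caveat.
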